### 7.7 Clinical reporting of research assay results

The results of the molecular assays are exploratory and are not intended to influence the individual patient's medical care. Findings will not be reported routinely to the responsible clinician except in the unlikely event that the result might be beneficial to the patient's clinical management.

### 7.8 Trial sample retention at end of study

The Chief Investigator has overall responsibility for custodianship of the trial samples. Laboratories are instructed to retain any surplus tumour samples pending instruction from the Chief Investigator on use, storage or destruction. It is possible that new or alternative assays may be of future scientific interest. At the end of the research study any surplus tumour samples may be retained for use in other projects that have received ethical approval. Hence, any surplus tumour samples may be transferred to a licensed tissue bank where they will be managed in accordance with

applicable host institution policies and the Human Tissue Act (HTA) requirements. Any excess blood samples will be destroyed once the study has been completed.

### 7.9 Withdrawal of consent for sample collection and/or retention

A patient may withdraw consent to take samples for research and/ or to retain and use their samples for research at any time without giving a reason. The Investigator must ensure that their wishes are recorded in the medical record and will inform the trials office accordingly. No further samples will be taken and any unused samples will be destroyed as per host institution policy.

## 8 INVESTIGATIONAL MEDICINAL PRODUCTS (IMPS)

Patients will be assigned to the appropriate BKM120 dose level according to the dose escalation scheme given below. BKM120 will not be dose escalated above 100mg od, as this dose has previously been established as the RPTD for future single agent studies (1). BKM120 will be supplied by Novartis and packaged, labelled and distributed by Fisher Clinical Services.

### 8.1 Dosing schedules: dose levels and BKM120 dose escalation plan

In this study, DLT is defined as the presence of the following:

1. Any  $\geq$  grade 3 non-haematological toxicity (excluding nausea, vomiting or diarrhoea) that requires hospital admission or which does not resolve to  $\leq$  grade 2 within 7 consecutive days of optimal treatment.
2. Any  $\geq$  grade 3 nausea, vomiting or diarrhoea will be considered DLT only if any of them persist for >48 hours despite maximum supportive care.
3.  $\geq$  Grade 3 pneumonitis
4. Any  $\geq$  grade 4 haematological toxicity.
5. Mood deterioration from baseline DLT will be any grade  $\geq 3$  mood change if BL score of 2. DLT will be any grade  $\geq 2$  mood change if BL score of  $\leq 1$ .

DLT will be considered to occur if the toxicity is attributed either to BKM120 or to its interaction with radiotherapy. Cohort 4 will only be opened if there is inadequate evidence that BKM120 alters tumour hypoxia or perfusion (see Section 12.1)

| DL                      | RT                                     | BKM120                      | BKM120 dose escalation plan                                                                                                                                                                                                                                                                                         |
|-------------------------|----------------------------------------|-----------------------------|---------------------------------------------------------------------------------------------------------------------------------------------------------------------------------------------------------------------------------------------------------------------------------------------------------------------|
| 1                       | 20Gy in 5 fractions
(days 8 - 14)   | 50 mg od
(days 1 to 14)  | Three patients will be entered
If 0/3 have DLT proceed to DL2
If 1/3 have DLT expand dose level to a total of 6 patients.
If none of the additional 3 patients develop DLT, proceed to DL2.
If any further patient(s) develop DLT ( $\geq 2/6$ ) the MTD is exceeded and the trial will be terminated.  |
| 2                       | 20Gy in 5 fractions
(days 8 - 14)   | 80 mg od
(days 1 to 14)  | Three patients will be entered
If 0/3 have DLT proceed to DL3.
If 1/3 have DLT expand dose level to a total of 6 patients.
If none of the additional 3 patients develop DLT, proceed to DL3.
If any further patient(s) develop DLT ( $\geq 2/6$ ) the MTD will be defined as 50mg od.                   |
| 3                       | 20Gy in 5 fractions
(days 8 - 14)   | 100 mg od
(days 1 to 14) | Three patients will be entered
If 0/3 have DLT then the MTD is 100 mg od.
If 1/3 have DLT expand dose level to a total of 6 patients.
If none of the additional 3 patients develop DLT, the RPTD is 100 mg bd.
If any further patient(s) develop DLT ( $\geq 2/6$ ) the MTD will be defined as 80mg od. |
| Expanded cohort at RPTD | 20Gy in 5 fractions
(days 8 - 14)   | MTD dose
(days 1 to 14)  | Once the MTD has been reached a further 6 patients will be treated at the MTD of BKM120 with palliative RT.                                                                                                                                                                                                         |
| 4                       | 20 Gy in 5 fractions
(days 22 – 28) | At MTD
(days 1 to 28)    | This cohort will only be used if there is no evidence of BKM120 induced changes in the tumour microenvironment on functional imaging in cohorts 1-3. A total of six patients will be entered into this cohort.                                                                                                      |

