## 6.1 Patient evaluability and replacement

### Dose escalation

The MTD will be based on DLTs observed within 6 weeks of completion of BKM120 treatment. DLTs will be assessed whilst the patient is on treatment and for up to 6 weeks after completion of treatment in all patients. Patients completing 14 days of BKM120 treatment who either complete the follow up period or withdraw early ~~from~~ experiencing DLT will be evaluable for dose escalation decisions. Patients who withdraw early for reasons other than experiencing DLT (e.g. progression) will be considered non-evaluable for dose escalation and replaced as necessary to complete each cohort. Patients replaced for dose escalation earlier than the 14 days will be followed up and considered evaluable for toxicity analysis.

### Expansion cohort and cohort 4

Secondary endpoints of changes in F-Misonidazole and in blood flow will be based on F-Miso PET-CT and perfusion CT scans prior to commencing BKM120 treatment and on the day that radiotherapy treatment commences. Patients who have data available from both scans will be considered evaluable for secondary endpoints. Patients withdrawn early or without scans will be considered non-evaluable for secondary endpoints and replaced as necessary to

complete each cohort. All patients who receive at least one dose of BKM120 will be followed up and will be considered evaluable for toxicity analysis.

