## 12.3 Other definitions of outcome:

**Toxic death:** Any death to which drug toxicity is thought to have a major contribution.  
**Early death:** Death during the first three weeks of treatment that is not a toxic death.

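### DLT items 1 and 2 together leave grade 4 or 5 nausea, vomiting or diarrhoea of 48 hours or less outside the DLT count, unless a separately graded complication qualifies

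*Protocol*

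**What the plan says.** The DLT definition appears three times with the same content: in the Protocol synopsis (primary endpoint), Section 3 and Section 8.1.

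- **Item 1** covers grade 3 or higher non-haematological toxicity, with an exclusion: "grade 3 non-haematological toxicity (excluding nausea, vomiting or diarrhoea) that requires hospital admission or which does not resolve to" grade 2 or lower within seven days.
- **Item 2** takes up the excluded toxicities, again from grade 3 upwards: "grade 3 nausea, vomiting or diarrhoea will be considered DLT only if any of them persist for >48 hours despite maximum supportive care".
- **Items 3 to 5** cover pneumonitis, haematological toxicity of grade 4 or higher (with no duration condition) and mood change.

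Section 12.3 defines toxic death as "Any death to which drug toxicity is thought to have a major contribution". No section says whether a toxic death is a DLT.

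Section 6.1 decides who counts for escalation: "Patients completing 14 days of BKM120 treatment who either complete the follow up period or withdraw early" because of DLT are evaluable. It adds: "Patients who withdraw early for reasons other than experiencing DLT (e.g. progression) will be considered non-evaluable for dose escalation and replaced as necessary". Section 17.1 puts into the dose-escalation analysis those who complete 56 days on trial or have a DLT. Sections 3 and 16.2 define the MTD by DLT counts alone.

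**The concern.** Item 2 starts at grade 3 and has no upper limit, so its 48-hour condition also governs grades 4 and 5. Its wording admits no other route to a DLT for these events, and item 1 has already given up its hospital-admission and seven-day routes for them.

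This sits badly with the rest of the definition. Any other non-haematological toxicity of grade 3 becomes a DLT once it needs admission. Grade 4 haematological toxicity is a DLT however brief. Life-threatening vomiting or diarrhoea that needs admission and settles within 48 hours is not.

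The gap concerns toxicities that the trial expects. Section 1.2 lists nausea, diarrhoea and vomiting among the most common BKM120 adverse events, and Section 13.4 lists nausea as an effect of thoracic radiotherapy.

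The DLT count is the primary endpoint and fixes the MTD, which is the dose given to the expansion cohort and to cohort 4. An event left out of the count moves the result towards a higher dose.

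**Working it through.** **Step 1. Apply the rules as written.** Take nausea, vomiting or diarrhoea of grade 4 or 5, lasting 48 hours or less, attributed to BKM120 or its interaction with radiotherapy, with no other qualifying event.

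- *Fatal.* No DLT item is met and follow-up is not completed. Under 6.1 the patient is non-evaluable and replaced. Under 17.1 the patient is outside the escalation analysis.
- *Life-threatening, drug stopped before day 14.* No DLT item is met. Under 6.1 the patient is non-evaluable and replaced. Section 8.4 keeps such a patient on scheduled visits, so 17.1 could instead admit the patient at day 56 as a non-DLT. The event is uncounted either way.
- *Life-threatening, with 14 days of drug and follow-up completed.* No DLT item is met. The patient is evaluable, stays in the denominator as a non-DLT and is not replaced.

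**Step 2. Effect at the decision boundaries.** If the patient is kept, one uncounted event turns 1/3 (expand to six) into 0/3 (proceed), or 2/6 (MTD exceeded) into 1/6 (tolerated).

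**Step 3. Effect on the chance of passing a dose level.** Under the Section 8.1 table a level passes with 0/3, or with 1/3 followed by 0/3. For a counted DLT probability p per patient:

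P(pass) = (1 − p)³ + 3p(1 − p)² × (1 − p)³

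Let d be the rate of other DLTs and s the rate of the short grade 4 or 5 events, taken as mutually exclusive. Then:

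- events counted as DLT: p = d + s
- as written, patient replaced: p = d/(1 − s)
- as written, patient kept as non-DLT: p = d

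The Protocol gives neither d nor s, so both are assumptions shown over a range.

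Example, d = 20%, s = 5%:

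- counted, p = 0.25: 0.4219 + 0.1780 = 0.600
- replaced, p = 0.20/0.95 = 0.2105: 0.4921 + 0.1937 = 0.686
- kept, p = 0.20: 0.5120 + 0.1966 = 0.709

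| d | s | Counted as DLT | As written, replaced | As written, kept as non-DLT |
|---|---|---|---|---|
| 10% | 2% | 0.871 | 0.903 | 0.906 |
| 10% | 5% | 0.814 | 0.897 | 0.906 |
| 10% | 10% | 0.709 | 0.887 | 0.906 |
| 20% | 2% | 0.665 | 0.700 | 0.709 |
| 20% | 5% | 0.600 | 0.686 | 0.709 |
| 20% | 10% | 0.494 | 0.660 | 0.709 |
| 30% | 2% | 0.454 | 0.482 | 0.494 |
| 30% | 5% | 0.396 | 0.462 | 0.494 |
| 30% | 10% | 0.309 | 0.428 | 0.494 |

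In every row the wording makes passing more likely, and keeping the patient as a non-DLT does so more than replacement.

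**Step 4. How often the gap could matter.** The Protocol's maximum for escalation reproduces as 6 × 3 = 18 evaluable patients, and the overall maximum as 18 + 6 + 6 = 30. Neither depends on this point. The chance of at least one such event in 18 patients is 1 − 0.98¹⁸ = 0.305 at s = 2% and 1 − 0.95¹⁸ = 0.603 at s = 5%.

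**The case against.** Several points on the other side are sound and limit the finding.

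- **Only three toxicities are affected.** A reader might infer that gastrointestinal toxicity in general escapes. It does not: oesophagitis, abdominal pain and the like remain under item 1.
- **Complications can still qualify.** Section 13.1 treats complications during a hospital stay as adverse events in their own right. A grade 3 or higher complication needing admission, such as dehydration, is a DLT under item 1. So it does not follow that every fatal case is missed. The gap remains because inclusion then depends on how the episode is coded.
- **Replacement is not general.** A reader might infer that the affected patient always leaves both numerator and denominator. Section 6.1 supports that only after death or early withdrawal.
- **Escalation is not automatic.** Section 16.1 makes absence of DLT a minimum criterion and allows review of emerging safety data. The Trial Management Group decides (8.7), with advice from the independent oversight committee (18.1). Deaths and life-threatening events are SAEs, reportable within 24 hours. Replaced patients stay in the toxicity analysis. These safeguards are real, but they are discretionary and do not alter an MTD defined on DLT counts.
- **Escalation is over.** Section 8.3 (Liver) says so, and the expansion cohort and cohort 4 have no rule based on a DLT count. This limits what a change can still influence. It does not settle whether the MTD and its reported DLT rates rest on a sound count.
- **The three statements of the definition agree.** There is no contradiction between them. The tension is within the definition (items 1, 2 and 4) and with 6.1 and 12.3.

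**Conclusion.** The point holds in a limited form. By wording alone, the primary endpoint can miss a life-threatening or fatal episode of nausea, vomiting or diarrhoea of 48 hours or less, provided no separately graded complication qualifies under item 1. The error always runs towards a lower counted DLT rate.

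Its size depends on a rate that the Protocol does not give. With 20% other DLTs, the chance of passing a dose level rises by 3.5 to 4.4 percentage points at a 2% event rate, 8.6 to 10.9 points at 5% and 16.6 to 21.5 points at 10%. The lower figure applies if all such patients are replaced, the higher if all are kept as non-DLTs. These are illustrations under stated assumptions; nothing in the Protocol shows that such an event occurred or that the MTD is wrong.

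**What to change.** Reconcile DLT items 1 and 2, Section 6.1 and the toxic-death definition in 12.3, and carry the same wording into the synopsis, Section 3 and Section 8.1. The result should be that the 48-hour condition does not, by its wording alone, exempt life-threatening or fatal events, and that the relation of a toxic death to DLT is stated. Which grades or durations are dose-limiting is a clinical threshold for the sponsor to set.

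Because escalation is complete, re-apply the reconciled definition to the recorded adverse events of all treated patients, and report DLT counts by dose level under both the current and the reconciled reading, including patients who were replaced.

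The cost is small: a short change of definition in three places, aligned text in 6.1 and 12.3, and one extra tabulation. Section 13.8 already requires onset, duration and worst grade on the CRF, and the current definition already needs the duration, so no new data collection is implied. The downside is that the DLT count may become slightly less favourable.

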| Primary Endpoint:                | 
Analysis of safety and identification of the maximum tolerated dose (MTD), which is defined as the highest dose at which no more than 1 of 6 evaluable patients or 0 of 3 evaluable patients experience a DLT. DLTs will be defined as per NCI CTCAE v 4.0. The following will be considered DLT if they occur at any point whilst the patient is on study:
 
 
Any <math>\geq</math> grade 3 non-haematological toxicity (excluding nausea, vomiting or diarrhoea) that requires hospital admission or which does not resolve to <math>\leq</math> grade 2 within 7 consecutive days of optimal treatment.
 
Any <math>\geq</math> grade 3 nausea, vomiting or diarrhoea will be considered DLT only if any of them persist for <math>>48</math> hours despite maximum supportive care.
 
<math>\geq</math> Grade 3 pneumonitis
 
Any <math>\geq</math> grade 4 haematological toxicity.
 
Mood deterioration from baseline (BL). DLT will be any grade <math>\geq 3</math> mood change if BL score of 2. DLT will be any grade <math>\geq 2</math> mood change if BL score of <math>\leq 1</math>.
 
                                                                                                                                                                                                                               |

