**Table of relevant clinical studies**

| Trial name/
researcher/
Pub. Ref. | Phase | Disease type                  | No. of
patients | Main
Toxicities                                                           | Outcome                                       |
|-----------------------------------------|-------|-------------------------------|--------------------|------------------------------------------------------------------------------|-----------------------------------------------|
| Bendell et al
(1)                    | I     | All advanced
solid tumours | 35                 | Hyperglycaemia,
upper abdominal
pain, rash, mood
alteration, nausea | MTD of
BKM120
established
(100mg od) |

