#### Dose escalation phase

Between 2 and 18 evaluable patients will be recruited to the dose escalation phase. The aim of this Phase I study is to define the MTD of BKM120 when used in combination with palliative thoracic radiotherapy. The starting dose will be 50mg od. Unless DLT occurs this will be escalated to 80mg od and then 100mg od. There will be no further dose escalation beyond 100mg od. The study uses a standard 3+3 cohort design. Three patients will be entered at each dose level. At minimum, the criteria for dose escalation will be that if, by 6 weeks after the 3rd patient in each cohort has completed treatment there is no DLT, then the study will proceed to the next dose level. There will be a continuous evaluation of safety data, and dose escalation will be reviewed in response to any emerging safety information, with the Chief Investigator reserving the right to prolong the duration between cohorts as appropriate. The first cohort of patients will be given the starting dose of 50mg od, consideration will be given to stopping the recruitment early whether 2 or 3 DLTs are observed – consequently the minimum number of patients recruited is 2. If no DLT is observed, 3 patients will be entered at the next higher dose level. If 1 DLT is observed, an additional 3 patients will be entered at the same dose level. This process will be repeated until MTD is reached. This is the dose level at which no more than 1 of 6 evaluable patients or 0 of 3 evaluable patients experience a DLT. As a result, the maximum number of evaluable patients that could be recruited is 18 (6 evaluable patients by 3 dose levels)

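### If the capped top dose level passes, the protocol names 100 mg od as the MTD even when no DLT has occurred at any dose; it has no outcome for an MTD not reached

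*Protocol*

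**What the plan says.** The synopsis gives the primary endpoint as safety, together with "identification of the maximum tolerated dose (MTD), which is defined as the highest dose at which no more than 1 of 6 evaluable patients" have a DLT; a first cohort of three without any DLT also qualifies. Sections 3, 16.1 and 16.2 repeat this definition. None of them requires a higher dose to have failed.

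The planned levels are 50, 80 and 100 mg od. Section 8 states that "BKM120 will not be dose escalated above 100mg od, as this dose has previously been established as the RPTD" for single-agent use, and section 16.1 repeats the cap: "There will be no further dose escalation beyond 100mg od". The table of relevant clinical studies in section 1.4 gives the single-agent result as "MTD of BKM120 established (100mg od)".

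The level 3 row of the table in section 8.1 has three outcomes:
- 0/3 DLTs: "If 0/3 have DLT then the MTD is 100 mg od".
- 1/3, then none in three more: "If none of the additional 3 patients develop DLT, the RPTD is 100 mg bd".
- At least 2/6: "the MTD will be defined as 80mg od".

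Two other places allow for no MTD being located. Section 16.1 opens its sample-size text with a condition that an MTD is reached. The level 1 row says that with at least 2/6 DLTs the MTD is exceeded and the trial ends, and it names no MTD.

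**The concern.** Finding the MTD of BKM120 with radiotherapy is the primary objective. If every level passes, the trial has a lower bound: the DLT limit was not crossed at the highest dose it was willing to give. The level 3 row turns that bound into a point identification.

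The label matters because 100 mg od is also the cited single-agent MTD. A report that the MTD with radiotherapy is 100 mg od would read as a toxicity limit that was looked for, found and left unchanged by radiotherapy. A run without a DLT cannot show this. The label is also carried forward, since the expansion cohort and cohort 4 are both defined by the MTD.

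The protocol deals with the opposite case, a limit below the tested range, by naming no MTD. It has no matching outcome at the top of the range.

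**Working it through.** **Inputs.** The cohort rules come from section 8.1: a level passes with 0/3, or with 1/3 followed by 0/3. The three levels and the cap come from sections 8 and 16.1. The protocol gives no true DLT rates, so a flat rate *p* of 2, 5, 10 or 15% at every level is assumed, with independent, evaluable patients.

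**The plan's own figures.** Maximum escalation size is 6 × 3 = 18 evaluable patients. With six in the expansion cohort and six in cohort 4, 18 + 6 + 6 = 30. Both agree with section 16.1.

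**The path without a DLT.** 0/3 at 50 mg, 0/3 at 80 mg and 0/3 at 100 mg uses 3 + 3 + 3 = 9 patients and ends in an MTD of 100 mg od.

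**Formulas.**
- Pass by 0/3: a = (1−p)³
- Pass by 1/6: b = 3p(1−p)² × (1−p)³
- Level passes: s = a + b
- Printed 0/3 branch at level 3 reached: s² × a
- Level 3 passes by either route (general definition): s³
- No DLT in nine patients: (1−p)⁹

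**Worked example, p = 5%.** a = 0.95³ = 0.857; b = 0.15 × 0.95⁵ = 0.116; s = 0.973. Then s² × a = 0.812, s³ = 0.922 and 0.95⁹ = 0.630.

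| Assumed flat DLT rate | Printed 0/3 branch gives MTD 100 mg od | Either passing route (general definition) | No DLT in nine patients |
|---|---|---|---|
| 2% | 93% | 98.6% | 83% |
| 5% | 81% | 92% | 63% |
| 10% | 60% | 74% | 39% |
| 15% | 41% | 54% | 23% |

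**Sensitivity to the flat rate.** With assumed rates rising over 50/80/100 mg, the probability of no DLT in nine patients is:
- 2/5/10%: 0.98³ × 0.95³ × 0.90³ = 0.59
- 5/10/20%: 0.32
- 5/15/30%: 0.18
- 10/20/33%: 0.11

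**What 0/3 supports.** The exact two-sided 95% upper limit for the DLT rate after 0/n is 1 − 0.025^(1/n). For n = 3 this is 1 − 0.292 = 0.708, or 71%. If the six expansion patients at that dose also had no DLT (0/9), the limit would be 34%. Section 17.5 summarises expansion safety descriptively, and the protocol gives no rule for revisiting the MTD label in the light of it.

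**The case against.** The strongest defence is that the protocol defines the MTD operationally, and consistently, as the highest dose with no more than 1/6 or 0/3 DLTs. The 0/3 branch applies that definition to a disclosed set of doses. This stands: there is no internal contradiction between the 0/3 branch and the definition, and nothing is miscalculated. What remains is that the definition lets an untested upper side count as a limit found.

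A second defence is that the cap is not arbitrary. It rests on the single-agent toxicity limit, and the stated worry is that radiotherapy adds toxicity. That is a fair reason for stopping at 100 mg od. It does not make the combination's limit an observed one; the synopsis itself notes that the drug is given for shorter periods here.

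Third, section 17.5 requires DLT counts and percentages by dose level, so a 0/3 would be visible beside the label. This softens the harm but leaves the primary conclusion worded too strongly.

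A reader might infer two stronger points that the documents do not support:
- *The table declares an MTD of 100 mg od whenever level 3 passes.* It prints that label only for 0/3. The 1/6 branch names an RPTD, printed as 100 mg bd; only the general definition supplies the MTD label there. That is why the two probability columns are kept apart.
- *The rule returns 100 mg od whatever the combination's true limit is.* It can also return 80 mg, 50 mg or termination. At a flat 20% DLT rate, level 3 passes by either route in only 36% of runs (s = 0.512 + 0.197 = 0.709; s³ = 0.356).

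**Conclusion.** The point holds as one of labelling and interpretation in the primary conclusion. Under the printed level 3 rule and the cap, the trial can name an MTD with no DLT at any dose, when the data support only that the DLT limit was not exceeded at the highest planned dose.

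This is a likely outcome if the combination is well tolerated: 63% for no DLT in nine patients at a flat 5% rate, and 39% at 10%. It becomes much less likely if toxicity rises steeply with dose. All these probabilities rest on assumed DLT rates; the existence of the path and the 71% upper limit after 0/3 do not. Sample size, doses and escalation decisions are unaffected.

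Separately, the 1/6 branch of the same row conflicts with the once-daily regimen, with the cap at 100 mg od and with the MTD label used elsewhere. Those passages must be reconciled.

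**What to change.** In the level 3 row of section 8.1, and in the MTD definition in the synopsis and sections 3, 16.1 and 16.2, state that if the highest planned level passes, the conclusion is *MTD not reached; highest planned dose tolerated*. Report it with the DLT count and its exact confidence interval. In the synopsis, section 2, the expansion and cohort 4 rows of section 8.1, and the other places that define those cohorts by the MTD, refer to *the MTD or, if not reached, the highest planned dose tolerated*.

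Leave the level 1 termination rule, all doses and all escalation steps as they are. In the same amendment, reconcile the level 3 1/6 branch with the regimen, cap and MTD wording elsewhere.

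The cost is an edit to wording and a less definite headline when the top level passes.

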| Blood test for pAkt measurement                                            | X                |        |                         | X                    | X      | X      | X      |
| Coagulation (INR)                                                          | X                |        |                         | X                    | X      | X      | X      |
| Urinalysis                                                                 | X                |        |                         |                      | X      |        | X      |
| Dispensing of BKM120                                                       |                  | X      |                         |                      |        |        |        |
| BKM120 a                                                        |                  |        | Once daily              |                      |        |        |        |
| Radiotherapy                                                               |                  |        |                         | 20 Gy in 5 fractions |        |        |        |
| Pregnancy test (if applicable)                                             |                  | X      | If clinically indicated |                      |        |        |        |

aBKM120 taken at 50mg, 80mg, 100mg (cohorts 1-3 respectively) or MTD (expansion cohort) once daily continuously on days 1-14

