| HbA 1c                                                          | X                |        |                         |       |        |                      |        |        |        |
| Liver Function Tests                                                       | X                |        |                         | X     | X      | X                    | X      | X      | X      |
| Blood test for pAkt measurement                                            | X                |        |                         | X     | X      | X                    | X      | X      | X      |
| Coagulation (INR)                                                          | X                |        |                         | X     | X      | X                    | X      | X      | X      |
| Urinalysis                                                                 | X                |        |                         |       | X      |                      | X      |        | X      |
| Dispensing of BKM120                                                       |                  | X      |                         |       |        |                      |        |        |        |
| BKM120 a                                                        |                  |        | Once daily              |       |        |                      |        |        |        |
| Radiotherapy                                                               |                  |        |                         |       |        | 20 Gy in 5 fractions |        |        |        |
| Pregnancy test (if applicable)                                             |                  | X      | If clinically indicated |       |        |                      |        |        |        |

aBKM120 taken at MTD once daily continuously on days 1-28

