### 16.2 Definition of primary and secondary endpoints

#### Dose escalation phase

The maximum tolerated dose (MTD) is defined as the highest dose of BKM120 in combination with radiotherapy at which no more than 1 of 6 evaluable patients or 0 of 3 evaluable patients experiences a DLT.

#### Expansion cohort and cohort 4

Changes in F-Misonidazole retention and in blood flow between pre and post BKM120 treatment are defined as response to BKM120 treatment based upon changes in tumour hypoxia and perfusion as detected by F-Miso PET-CT scans and perfusion CT scans respectively. Each patient will be classified as a 'responder' or 'non-responder' on the basis of their pre- and post- BKM120 imaging. Those patients whose imaging demonstrates the presence of a physiological response on either perfusion CT and/or F-Misonidazole PET-CT will be classified as a responder whilst those that do not show a response on either imaging modality will be classed as a non-responder.

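### The dose-escalation table names 100 mg twice daily after 1/6 DLTs at dose level 3, where the protocol's own MTD rule gives 100 mg once daily

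*Protocol*

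**What the plan says.** Sections 2 and 5.3 send the reader to Section 8.1 for how the MTD is determined. In the table there, the dose level 3 row gives BKM120 100 mg od on days 1 to 14 and has three outcomes:

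- No DLT in three patients: "If 0/3 have DLT then the MTD is 100 mg od".
- One DLT in the first three and none in the next three: "If none of the additional 3 patients develop DLT, the RPTD is 100 mg bd".
- Two or more DLTs in six: the MTD is 80 mg od.

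The next row is headed "Expanded cohort at RPTD", but its dose column and its text both refer to the MTD.

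Elsewhere the protocol sets a ceiling. Section 8 says: "BKM120 will not be dose escalated above 100mg od, as this dose has previously been established as the RPTD". Section 16.1 says: "There will be no further dose escalation beyond 100mg od". Section 16.2 defines the MTD as "the highest dose of BKM120 in combination with radiotherapy at which no more than 1 of 6 evaluable patients", or none of three, has a DLT; the synopsis and Sections 3 and 16.1 use the same limits.

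**The concern.** The second outcome differs from the rest of its row in two ways. It changes the frequency from od to bd, which doubles the daily dose to one that no cohort receives. It also changes the label from MTD to RPTD, so read literally this branch declares no MTD at all. The MTD is the primary endpoint, and it sets the dose for the expansion cohort and for cohort 4.

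The table is the operative decision rule, and it is the text against which a reader of the final report would check the declared MTD. What is at stake is therefore the correctness of that rule and record: the dose, the frequency and the label.

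**Working it through.** **1. What the MTD rule gives.** The inputs are the MTD definition (Sections 3, 16.1 and 16.2), the dose level 3 dose of 100 mg od (Section 8.1 and synopsis) and the ceiling of 100 mg od (Sections 8 and 16.1). One DLT in six meets the limit of no more than 1 of 6. No higher dose is tested. The MTD is therefore 100 mg od. No other part of the protocol spells out this particular branch; the result follows from applying the definition.

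**2. Size of the discrepancy.**

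- As written: 2 × 100 mg = 200 mg a day.
- By the rule: 1 × 100 mg = 100 mg a day.
- Ratio: 200 / 100 = 2.

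The clinical pharmacokinetics text in Section 1.2 cites doses of 12.5 to 150 mg, so 200 mg a day also lies above the range described there.

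**3. Frequency elsewhere.** The schedule footnote for cohorts 1-3 and the expansion cohort reads "or MTD (expansion cohort) once daily continuously on days 1-14". The cohort 4 footnote reads "BKM120 taken at MTD once daily continuously on days 1-28". Section 8.2 instructs patients to take one dose each morning. None of these allows for a twice-daily MTD.

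**4. Capsule supply.** The inputs are 50 mg capsules at 35 per bottle (Section 11.1) and bottles per patient at the 100 mg level (Section 11.6). At 50 mg per capsule, 100 mg od is 2 capsules a day and 100 mg bd is 4. Capsules needed = capsules per day × days.

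| Cohort at 100 mg | Days | Dispensed | od needs | bd would need |
|---|---|---|---|---|
| Expansion | 14 | 1 × 35 = 35 | 2 × 14 = 28 | 4 × 14 = 56 |
| Cohort 4 | 28 | 2 × 35 = 70 | 2 × 28 = 56 | 4 × 28 = 112 |

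Only once-daily dosing fits the supply in either cohort.

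**5. How often the branch would apply.** If dose level 3 is opened and p is the true DLT probability there, the chance of one DLT in the first three and none in the next three is 3p(1−p)² × (1−p)³ = 3p(1−p)⁵. The protocol gives no value for p, so the range below is an assumption.

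| p | Probability of the branch |
|---|---|
| 0.05 | 0.116 |
| 0.10 | 0.177 |
| 0.20 | 0.197 |
| 0.30 | 0.151 |
| 0.40 | 0.093 |

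At the design stage this was an ordinary outcome of a 3+3 scheme.

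**6. Sample size.** The stated maxima reproduce as 6 × 3 = 18 for escalation and 18 + 6 + 6 = 30 in total. The error does not affect them.

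**The case against.** The best case against making much of this is that the slip is harmless. Two sections cap the dose at 100 mg od, the row's own dose column says od, and the schedules and Section 8.2 require once-daily dosing. Section 5.3 ties the expansion cohort to the dose of one of cohorts 1-3, and the pharmacy would not dispense enough capsules for bd. The liver guidance in Section 8.3 also refers to the escalation phase as completed, so at this version the branch governs no future escalation decision. A reader of the whole protocol would neither dose nor declare 100 mg bd.

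The label can be defended too. The protocol calls the same single-agent dose the MTD in Section 1.4 and the RPTD in Sections 1.2 and 8. The expansion row says in its own text that patients are treated at the MTD, whatever its heading.

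Most of this stands. No dosing hazard is shown, no estimate or sample size changes, and the row heading alone would be a matter of tidiness. It is also an inconsistency of wording rather than a miscalculation. What the objection does not remove is that Section 8.1 is where the protocol places the rule for its primary endpoint, and one terminal branch of that rule is incorrect. Completed escalation does not settle the matter either, because the table remains the written basis for the MTD used in the expansion cohort and cohort 4.

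**Conclusion.** The concern holds. One of the three outcomes at dose level 3 states a daily dose of 200 mg where the protocol's own definition and ceiling give 100 mg, and it labels that dose RPTD instead of MTD. The conclusion rests on applying the stated MTD definition to the top dose level and needs no outside figure. The assumed DLT rates serve only to show that the branch could be reached. The most likely explanation is a typing error of bd for od. The consequence is a wrong rule and record for the primary endpoint that should be corrected, with no demonstrated risk to patients.

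**What to change.** In the dose level 3 row of the Section 8.1 table, reword the second outcome to: *If none of the additional 3 patients develop DLT, the MTD is 100 mg od.* In the following row, change RPTD to MTD in the heading so that it matches the dose column and text. These are two wording corrections in one table, with no change to design, sample size, analysis or drug supply.
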